### EBRT treatment planning

The EBRT component of the treatment package will follow the SBRT. CTVebrt will be at the discretion of the treating clinician. For ECE, a 3 mm margin around the prostate is recommended, excluding the rectal wall. For SVI if no gross T3b disease is detected, the proximal 20 mm of the seminal vesicle should be included. For Lymph-node invasion (LNI), the pelvic nodal RT is recommended if the LNI risk is > 15% as indicated by the MSKCC Prostate Nomogram. If treated, pelvic nodes shall be contoured as per the Radiation Therapy Oncology Group (RTOG) guidelines with a superior limit of the bifurcation of the common iliac arteries, and excluding the pre-sacral nodes as reflected by current surgical recommendations of the extent of an extended lymph node dissection [18]. CTVebrt to PTVebrt expansion will be 5–7 mm, or 7 mm if gross SVI is present around this structure in particular.

46Gy in 23 fractions will be prescribed to 95% of the PTVebrt as per ICRU 83. An IMRT, VMAT or Tomotherapy technique is recommended. Dose constraints are outlined in the accompanying Table 3.

**Table 3 Tab3:** Phase two EBRT component dose constraints

Structure	Per-Protocol	Minor Variation	Major Variation
PTVebrt D95	> 46 Gy	44–46 Gy	< 44 Gy
Prostatic Urethra PRV	Dmax < 47 Gy	Dmax: 47–50 Gy	Dmax > 50 Gy
Small Bowel	Dmax < 47 Gy	Dmax: 47–50 Gy	Dmax > 50 Gy
Neck of Femur	Dmax < 35 Gy	Dmax: 35–45 Gy	Dmax> 45 Gy
Rectum V45	< 25%	25–35%	> 35%
Bladder V45	< 25%	25–35%	> 35%

### Treatment delivery

Due to potential volume changes during a course of EBRT, as well as evidence of volume changes after HDRB, all patients should receive the boost component of their therapy prior to the fractionated EBRT component [19, 20].

The two SBRT boost fractions are to be separated by a 1 week break. The EBRT component is then to commence 2 weeks after the final boost fraction.

Preparation: Patient to continue same bladder preparation and enema regimen as used during simulation. Use Rectafix™ if utilised during simulation.

IGRT: On-line correction to gold fiducials, prostate and IDC with 0 mm action threshold. All effort should be made to commence treatment as soon as feasible after pre-treatment imaging has been performed.

During SBRT treatment: For techniques where real-time tracking or position monitoring is available (e.g. CK kV or intraprostatic transponders) this should be used. For other approaches, aim to perform repeat orthogonal imaging at least every 4 min, as there is evidence to support that 95% of patients will experience less than 3 mm of intrafraction motion over this timeframe [21]. Since most intrafraction motion will be either in the inferior-superior or anterior-posterior planes, only a lateral Electronic Portal Imaging (EPI) is necessary during treatment [22, 23].

### Data collection

Patients will be assessed at baseline, the completion of treatment, 6 weeks post treatment, and then six monthly thereafter up to 5 years. At all visits, CTCAE GI and GU toxicity will be recorded. PSA will be measured at baseline, and then at all visits following treatment. The main efficacy endpoint is bNED calculated by the Phoenix definition of nadir+ 2 [24]. Any disease relapses or initiation of salvage treatments will also be recorded. Patient related quality of life (EPIC-26), and questionnaires regarding tolerance of treatment will also be collated at baseline, end of treatment, 12 months, 36 months and 60 months.

### Sample size

The actuarial rates of CTCAE late grade 2–3 GI and GU toxicity will be calculated and reported at the 5 year mark. Studies using HDRB boost as well as IG-IMRT suggest rates of 5–15% are achievable. The study will be powered to recruit sufficient numbers to be confident that < 15% of men will have either a grade 2–3 GI or grade 2–3 GU late GU event. The formula is:$$ \mathrm{n}=\left(1.96/\mathrm{E}\right)2\ \mathrm{p}\left(1\hbox{-} \mathrm{p}\right) $$

Where E is the margin of error. A conservative upper estimate of p here is 0.225 (the probability of an event). E might be 0.05 since that at worst gives a 95% CI as 0.15+/− 0.05. With these figures *n* = 268.

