### Objectives

The primary objectives of the study are to determine the safety and efficacy of a SBRT prostate boost. Safety will be established if the cumulative rate of either acute or late GI or GU toxicity is equivalent to or less than previously reported in the HDRB or dose escalated IGRT EBRT literatures. Efficacy will be assessed via biochemical control after 3 years.

The secondary objective of the study is to ensure that the rates of grade 3 or higher acute CTCAE GI or GU toxicity does not increase with increasing dose delivery to the Clinical Target Volume (CTV).

Multicentre feasibility will be demonstrated if 3 or more centres contribute 5 or more patients to the study.

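### The late-toxicity event used for sizing and reporting stops at grade 3, so a man whose only late event is grade 4 or 5 would not be counted

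*Protocol article*

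**What the plan says.** The Sample size section states the reported late endpoint: "The actuarial rates of CTCAE late grade 2–3 GI and GU toxicity will be calculated and reported at the 5 year mark". It then says the trial should recruit enough men to "be confident that < 15% of men will have either a grade 2–3 GI" event or its genitourinary counterpart; the full event is "either a grade 2–3 GI or grade 2–3 GU late GU event". The band is given as grade 2–3 both times. The benchmark beside it is "Studies using HDRB boost as well as IG-IMRT suggest rates of 5–15% are achievable".

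Elsewhere the article treats grades differently:

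- **Objectives, acute toxicity:** the aim that severe acute toxicity should stay level as dose rises is set out in a sentence that opens "The secondary objective of the study is to ensure that the rates of grade 3 or higher acute CTCAE GI or GU toxicity does not". This wording is open at the top.
- **Objectives, safety:** the safety criterion covers acute and late toxicity and names no grade.
- **SBRT treatment planning, escalation mechanism:** a single acute grade 4 episode at a dose level is enough to fail the escalation condition.
- **Discussion:** severe toxicity is named as the endpoint given priority when the patient numbers were worked out.
- **Data collection:** "At all visits, CTCAE GI and GU toxicity will be recorded", with no upper limit on grade.

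**The concern.** A safety endpoint normally has a floor and no ceiling. With a ceiling at grade 3, the late rate can leave out the worst outcomes. A man whose first and only late event is grade 4 would stay event-free in the actuarial curve, and a man who died of late toxicity with no earlier grade 2–3 record would be censored. The reported rate would then be lower than the rate of moderate-or-worse late harm that most readers would take it to be.

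This matters here because the late rate supports the claim that a dose-escalated boost is safe, and because the article says its numbers were chosen with severe toxicity in mind. It is a problem in what the text states, not an omission. A later analysis plan that counted grades 4 and 5 would have to depart from the definition printed here.

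**Working it through.** **1. The plan's own figure.** Inputs from the Sample size section: p = 0.225 ("A conservative upper estimate of p here is 0.225 (the probability of an event"), E = 0.05 ("E might be 0.05 since that at worst gives a 95% CI as 0.15+/− 0.05") and z = 1.96. The 2 in the printed formula is read as an exponent lost in typesetting.

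n = (1.96/0.05)² × 0.225 × 0.775 = 1536.64 × 0.174375 = 267.95, which rounds up to 268. The stated figure reproduces.

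**2. The wording side by side.**

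| Place | Toxicity | Upper end |
|---|---|---|
| Sample size (twice) | late | closed at grade 3 |
| Objectives, secondary | acute | open (grade 3 and above) |
| Escalation mechanism | acute | grade 4 named as decisive |
| Objectives, safety | acute and late | no grade given |
| Discussion | sizing rationale | severe toxicity |

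No entry says how a late grade 4 or 5 event enters the late rate.

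**3. How many men could be missed.** The article gives no rate of late grade 4–5 toxicity, so a range is assumed. The counts are upper bounds, because they suppose that none of these men also has a recorded late grade 2–3 event.

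| Assumed rate q | Expected men, 268 × q | Chance of at least one, 1 − (1 − q)^268 |
|---|---|---|
| 0.5% | 1.3 | 74% |
| 1% | 2.7 | 93% |
| 2% | 5.4 | 99.6% |

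In a trial of this size the question would probably arise, but for only a few men.

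**4. Effect on the sample size.** Adding q to p = 0.225 with E kept at 0.05:

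- q = 0.5%: p = 0.230, n = 1536.64 × 0.230 × 0.770 = 272.1, so 273
- q = 1%: p = 0.235, n = 1536.64 × 0.235 × 0.765 = 276.2, so 277
- q = 2%: p = 0.245, n = 1536.64 × 0.245 × 0.755 = 284.2, so 285

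If n stays at 268, the half-width at p = 0.245 is 1.96 × √(0.245 × 0.755/268) = 0.0515, against 0.0500 at p = 0.225. The loss of precision is negligible.

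**The case against.** The best defence is that the band was chosen to match the literature. The Background reports published late rectal toxicity in the same grade 2–3 band (26% in a randomised study, about 6% in single-institution reports), and the safety objective is a comparison with published series. A matching category makes that comparison cleaner. This stands as a reason to report the grade 2–3 rate, but not as a reason to leave grades 4 and 5 out of the main event, since both rates can be shown.

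Three further points reduce the size of the problem:

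- Toxicity is recorded at every visit without a cap. A reader might infer that late grade 4–5 events are lost to the trial. They are not; they are only outside this endpoint.
- A man with a grade 4 event is missed only if no late grade 2–3 event was also recorded for him, so the counts above are upper bounds on an assumed rate.
- The open-ended wording in Objectives and the grade 4 rule for escalation concern acute toxicity. They show that the authors write an open upper end when they mean one, but they do not directly contradict the late definition. The real tension is with the sizing rationale in the Discussion.

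A reader might also infer that the event ignores baseline, so that stable pre-existing grade 2 symptoms count as late events. The article does not support this. It does not say whether late events are absolute grades or worsening from baseline. It does collect grades at baseline, and this kind of rule is commonly left to the full protocol or analysis plan, neither of which is shown. Any count of men affected would need a baseline prevalence and a counting rule that the article does not give.

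**Conclusion.** The point holds for the grade ceiling only. As written, the late event that the trial is sized on and will report excludes a man whose only late event is grade 4 or 5, and this sits badly with the stated priority on severe toxicity. The authors may well have meant grade 2 or higher, but the text does not say so.

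The size is at most about 1 to 5 of 268 men, resting on an assumed 0.5–2% rate of late grade 4–5 toxicity and on none of these men having a recorded grade 2–3 event. The effect on n is small, and the arithmetic behind 268 is correct. The case for changing the definition is that the few men left out are those with the worst harms, not that the trial is too small.

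**What to change.** In the Sample size section, define the late event as CTCAE gastrointestinal or genitourinary toxicity of grade 2 or higher, stating that grades 4 and 5 are included, and use the same definition for the 5-year actuarial rate. Report late grade 3 or higher on its own line. Where published comparators use the grade 2–3 band, show that rate beside the main one, labelled as a comparison.

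The cost is wording and one or two extra lines in a results table. The grades are already collected at every visit, so no new data are needed, and the sample size need not be reopened for this reason.

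### The 268 men are sized for a margin of error, not for showing a late toxicity rate below 15%, and the interval of 0.15 ± 0.05 does not match the inputs

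*Protocol article*

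**What the plan says.** All of this stands in the Sample size section of the protocol article.

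- Endpoint: actuarial rates of late grade 2–3 GI and GU toxicity, which "will be calculated and reported at the 5 year mark".
- Background rates: "Studies using HDRB boost as well as IG-IMRT suggest rates of 5–15% are achievable".
- Aim: "The study will be powered to recruit sufficient numbers to be confident that < 15% of men will have either a grade 2–3 GI" or GU late event.
- Method: n = (1.96/E)² p(1 − p), with E the margin of error. The 2 is printed on the line and is read here as a square.
- Inputs: "A conservative upper estimate of p here is 0.225 (the probability of an event"; and "E might be 0.05 since that at worst gives a 95% CI as 0.15", plus or minus 0.05.
- Result: "With these figures *n* = 268".

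The section gives no numerical power, no single assumed true rate below 15%, and no rule for when a rate below 15% would be concluded. The Objectives section makes safety a primary objective, and the Discussion says that the toxicity risk took priority in setting the patient numbers.

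**The concern.** Two things do not fit together.

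First, the calculation uses a rate of 22.5% but its result is described by an interval around 15%. No single value of p gives both 268 and 0.15 ± 0.05.

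Second, and more important, the formula answers a different question from the one asked. A margin-of-error formula says how wide the interval will be around whatever rate is observed. It does not say how likely that interval is to lie wholly below 15%. The section nevertheless presents the study as powered for that claim.

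This is the only sizing argument in the article, and it serves a primary objective. A reader could take an observed rate of 15%, with the described interval around it, as the result the trial was designed to deliver. That result would not support the stated aim. Nor can the reader tell what observed rate would.

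**Working it through.** **Inputs from the Sample size section:** multiplier 1.96, p = 0.225, E = 0.05, threshold 15%, rates thought achievable 5–15%, n = 268.

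**1. Reproduce the plan's figure.** (1.96/0.05)² = 39.2² = 1536.64. Then 1536.64 × 0.225 × 0.775 = 267.95, rounded up to 268. The number follows from its inputs.

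**2. Size for the interval described.** 1536.64 × 0.15 × 0.85 = 195.9, so 196.

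**3. Intervals that 268 men give.** Half-width = 1.96 × √(p(1 − p)/268).

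| Observed rate | Half-width | 95% interval |
|---|---|---|
| 22.5% | 0.0500 | 17.5% to 27.5% |
| 15% | 0.0428 | 10.7% to 19.3% |
| 10% | 0.0359 | 6.4% to 13.6% |

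At 22.5% the whole interval lies above the threshold, and at 15% the interval contains it.

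**4. What would exclude 15%.** As an approximation, take all 268 men as followed for 5 years and the endpoint as a simple proportion. The upper limit of the two-sided exact (Clopper-Pearson) 95% interval is below 15% with at most 28 events (28/268 = 10.4%, upper limit 14.7%). The Wilson interval gives the same cut-off. A one-sided 95% exact limit allows 30 events (30/268 = 11.2%, upper limit 14.9%).

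**5. Chance of reaching that.** This is the binomial probability of at most 28 or at most 30 events among 268.

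| True rate | Two-sided limit (≤28) | One-sided 95% limit (≤30) |
|---|---|---|
| 5% | about 100% | about 100% |
| 7.5% | 97% | 99% |
| 9% | 83% | 91% |
| 10% | 64% | 78% |
| 12% | 25% | 39% |
| 15% | 2% | 4% |
| 22.5% | about 0% | about 0% |

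**6. For scale.** The one-sample normal-approximation formula is n = [(1.96 √(0.15 × 0.85) + 0.84 √(p₁(1 − p₁)))/(0.15 − p₁)]², for 80% power and one-sided 0.025. It gives 246 men at an assumed true rate p₁ of 9% and 363 at 10%. So 268 corresponds roughly to a design alternative of 9%, which the section does not mention.

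**The case against.** The strongest defence is that 0.225 was never meant as the expected rate. It is labelled a cautious upper value, and the rates thought achievable are 5–15%. Sizing on a larger p inflates the variance and guarantees a half-width of no more than 5 points at any rate up to 22.5%. On that reading ± 0.05 is a true upper bound at 15%, where the actual half-width is 4.3 points, and the 268 − 196 = 72 additional men are a margin. This is coherent and may be what was intended, although the section does not spell it out. It softens the mismatch of inputs. It does not turn a bound on the width into power to exclude 15%.

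A reader might infer that 268 is miscalculated or too small, or that 268 men can never show a rate below 15%. The document does not support either reading. The arithmetic is right, and no sound design should conclude a rate below 15% when the true rate is 15% or 22.5%, so failure at those two values is no fault of the sample size. In the lower part of the plan's own 5–15% range the chance of success is high.

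Two further objections also have force. Sizing for precision is legitimate in a phase 2 trial, and a detailed decision rule may be left to an analysis plan that is not shown. The point here rests on what is printed: a claim of power that the printed formula does not deliver. And because the endpoint is an actuarial 5-year rate, a raw count such as 28/268 cannot serve as the rule. With censoring, the count does not determine the upper limit.

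**Conclusion.** The point holds as a mismatch between aim, inputs and described result, not as an error in the number. The phrase "powered to recruit sufficient numbers to be confident that < 15% of men" claims a property that the formula does not provide, and at best ± 0.05 is a conservative bound on the half-width.

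In size, the difference matters within the plan's own range. Between true rates of 10% and 15%, the chance of supporting the claim falls from 64% to 2% with a two-sided limit, or from 78% to 4% with a one-sided limit. The choice of limit moves the cut-off by two events and does not change the conclusion. These chances assume 268 evaluable men with complete 5-year follow-up. Censoring would reduce precision and so lower the chance of success at true rates below 15%.

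**What to change.** Keep n = 268 and change the wording in three places.

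1. Replace the sentence that describes the interval as 0.15 ± 0.05 at worst with: 268 men give a 95% confidence interval half-width of 5.0 percentage points if the rate is 22.5% and 4.3 points if it is 15%.
2. Replace the claim of power with an explicit rule: a late toxicity rate below 15% is concluded only if the upper limit of the 95% confidence interval of the 5-year actuarial rate is below 15%. State whether that limit is one-sided or two-sided.
3. Add the operating characteristics for the chosen limit, labelled as an approximation that assumes complete 5-year follow-up. For a two-sided exact limit: about 97%, 83%, 64%, 25% and 2% at true rates of 7.5%, 9%, 10%, 12% and 15%. For a one-sided 95% limit: about 91%, 78% and 39% at 9%, 10% and 12%. Give the counts of 28 and 30 events only as illustrations, and note that censoring lowers the chance of success.

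The cost is wording only, with no extra patients and no change in procedures. The downside is that the stated capability of the trial becomes less favourable than the present text suggests.

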#### Feasibility

The protocol is deemed to be feasible if all of the following criteria are met:At least 3 different centres participate.Each centre accrues at least 5 patients.At least two centres attempt dose escalation.

## Discussion

Several randomized controlled trials have demonstrated superior outcomes of a brachytherapy boost approach for intermediate and high risk PC compared with EBRT alone [25, 26]. Despite this, the use of brachytherapy continues to regress [27]. Concurrently, the wider availability of new technology has created an opportunity to try to replicate brachytherapy boost type radiotherapy treatment plans which can be delivered using standard EBRT equipment. The higher daily doses in the SBRT component are potentially very harmful to normal tissues, hence meticulous attention has been made in this study to minimise the risks to patients. Although three main endpoints are noted, it is the risk of severe toxicity which is prioritized in calculating the necessary patient numbers.

The management of such men is complicated by the integration of ADT, the investigation of newer agents, and the simultaneous investigation of SBRT monotherapy. The PROMETHEUS trial explores whether optimisation of the EBRT component is possible by translating the HDRB boost regimen into a non-invasive equivalent which can be more widely deployed. The structure of a future randomized trial is difficult to predict given the ongoing evolution in practice, however the PROMETHEUS schedule could be flexibly combined with various non-cytotoxic agents given the freedom to do so in the protocol.

## Abbreviations

ABR: Alpha/beta ratio
ADT: Androgen deprivation therapy
AE: Adverse event
ARTG: Australian register of therapeutic goods
bNED: Biological non-evidence of disease
CBCT: Cone beam computerised tomography
CK: Cyberknife
CT: Computerised tomography
CTC AE: Common terminology criteria for adverse events
CTV: Clinical target volume
DRE: Digital rectal examination
EBRT: External beam radiation therapy
ECE: Extracapsular extension
ECOG: Eastern Cooperative Oncology Group
EPI: Electronic portal imaging
GI: Gastro intestinal
GU: Genito urinary
HDRB: High dose rate brachytherapy
ICRU: International commission of radiation units and measurements
IDC: In-dwelling urinary catheter
IGRT: Image guided radiation therapy
IMRT: Image guided radiation therapy
KV: Kilovoltage
LDRB: Low dose rate brachytherapy
MRI: Magnetic resonance imaging
MSKCC: Memorial sloan kettering cancer center
MV: Megavoltage
MVCT: Megavoltage computerised tomography
NOF: Neck of femur
OAR: Organ at risk
PC: Prostate cancer
PCSS: Prostate cancer specific survival
PRV: Planning target at risk volume
PSA: Prostate specific antigen
PTV: Planning target volume
QA: Quality assurance
RDD: Rectal displacement device
RT: Radiation therapy
RTOG: Radiation therapy oncology group
SBRT: Stereotactic body radiotherapy
SVI: Seminal vesicle invasion
VMAT: Volumetric modulated arc therapy
